# Clinical efficacy of Jianqiao ancient moxibustion in treating chronic fatigue syndrome: a single-center randomized controlled superiority trial protocol

**DOI:** 10.3389/fmed.2026.1860390

**Published:** 2026-06-26

**Keywords:** ancient moxibustion, chronic fatigue syndrome, infrared thermal imaging, protocol, randomized controlled superiority trial

## Abstract

**Background:**

Chronic fatigue syndrome (CFS) is a widespread and debilitating disorder that profoundly impacts the physical and mental health of patients. In traditional Chinese medicine (TCM), spleen–kidney yang deficiency is recognized as the most prevalent syndrome associated with CFS. Moxibustion is commonly employed to mitigate fatigue and address yang deficiency; however, conventional moxa box moxibustion has demonstrated limited clinical efficacy in practice. Considering the intrinsic benefits of Jianqiao ancient moxibustion in terms of its herbal formula and treatment coverage, this randomized controlled superiority trial aims to compare the clinical efficacy of Jianqiao ancient moxibustion with that of moxa box moxibustion in patients with CFS who exhibit a spleen–kidney yang deficiency pattern.

**Methods:**

This single-center, single-blind randomized controlled superiority trial will enroll 90 eligible patients diagnosed with CFS exhibiting a spleen–kidney yang deficiency pattern. Participants will be randomly assigned in a 1:1 ratio to receive either Jianqiao ancient moxibustion or moxa box moxibustion, with each group receiving standardized interventions as outlined in the trial protocol. Each 60-min treatment session will be administered three times per week for 4 consecutive weeks. A follow-up assessment will be conducted at week 16. The primary outcome measure will be the Fatigue Scale-14. Secondary outcome measures will include the Spleen–Kidney Yang Deficiency Symptom Scale, the Self-Rating Anxiety Scale, the Self-Rating Depression Scale, and infrared thermal imaging. All evaluations will be performed at baseline, immediately post-intervention at week 4, and during follow-up at week 16.

**Discussion:**

It is hypothesized that Jianqiao ancient moxibustion will be more effective than moxa box moxibustion in alleviating symptoms in patients with CFS who have spleen–kidney yang deficiency. Furthermore, this study will employ infrared thermal imaging to assess alterations in the thermal characteristics of the Sanjiao and Governor Vessel both prior to and following moxibustion. This methodology may help elucidate the mechanisms underlying moxibustion’s modulation of yang-qi distribution in patients with CFS.

**Study protocol registration:**

https://www.chictr.org.cn/showproj.html?proj=193045.

## Introduction

1

Chronic fatigue syndrome (CFS) is a common idiopathic disorder characterized by unexplained fatigue that persists for at least 6 months. In addition, it is accompanied by at least four secondary symptoms, including unrefreshing sleep, prolonged post-exertional malaise, impairment of concentration or short-term memory, sore throat, tender lymph nodes, multi-joint and muscle pain, and headaches (1). The exact pathogenesis of CFS has yet to be fully elucidated. Nevertheless, existing evidence suggests the potential implication of infectious agents, psychological stressors, metabolic disturbances, and genetic predispositions. Furthermore, functional abnormalities in the immune, neural, endocrine, and intestinal microbiota systems are implicated in the pathophysiology of CFS (2, 3). Globally, an estimated 1.7 to 24 million individuals are affected by CFS, with approximately 836,000 to 2.5 million of these individuals residing in the United States. Epidemiological data indicate that the estimated prevalence of CFS is 0.89% according to the Fukuda criteria, with female participants affected approximately 1.5 times more frequently than male individuals (4, 5). In China, the estimated prevalence of CFS in the general population is 12.54%, with a similarly high prevalence observed among female individuals (6). Clinically, between 10 and 25% of patients experience impaired mobility, 25.7% lose their working capacity, and 16.2% are severely confined to bed, requiring long-term care (7). Due to its debilitating physical and cognitive symptoms, which are exacerbated by activity, CFS also imposes significant socioeconomic burden (8). At present, while the symptoms of CFS can be managed, there remains no definitive cure for the condition, whether through pharmacological or non-pharmacological means. According to the 2021 NICE guidelines, essential management strategies encompass energy management, the integration of physical activity and exercise, symptomatic treatment, and multidisciplinary care. Importantly, in contrast to the 2007 NICE guidelines, the updated 2021 guidelines advise against using graded exercise therapy for CFS and clarify that cognitive behavioral therapy is not curative (9, 10). Consequently, there continues to be a pressing clinical demand for the development of innovative and efficacious therapies for CFS.

Traditional chinese medicine (TCM) does not have a distinct term for CFS; instead, it is categorized under consumptive disease based on clinical manifestations (11). The central pathogenesis of this condition is identified as yang-qi deficiency (12). Importantly, within TCM, the kidney is considered the congenital foundation and the spleen is considered the acquired foundation of the human body. Consequently, a deficiency in spleen–kidney yang-qi can result in impaired visceral function (13). Furthermore, spleen–kidney yang deficiency syndrome is the most prevalent pattern observed in the clinical syndrome differentiation of CFS (14). As a traditional non-pharmacological therapy within TCM, moxibustion has historically been considered a primary intervention for consumptive diseases (15). This technique involves the combustion of moxa wool to provide thermal stimulation to the body surface. It regulates the balance of qi and blood by warming the meridians, unblocking collaterals, and enhancing qi and blood circulation, ultimately restoring the body’s yang-qi vitality (16). Numerous studies have demonstrated its significant efficacy in patients with CFS, showing substantial alleviation of fatigue, depressive mood, sleep disturbances, and other related symptoms (17).

Conventional moxa box moxibustion demonstrates partial efficacy in the treatment of CFS; however, it is limited by restricted treatment coverage, suboptimal thermal penetration, and incomplete symptomatic improvement. Jianqiao ancient moxibustion is a distinctive form of moxa stick moxibustion recognized as a representative element of traditional medicine and as an intangible cultural heritage of Hangzhou, Zhejiang Province (18). This practice employs a proprietary formula that integrates southern herbs, known as “Jian Shiba,” with northern moxa, as detailed in Table 1. Furthermore, it incorporates specialized traditional processing techniques, including herbal decoction, natural sun-drying, and manual pounding into moxa floss (19). The resulting product comprises two large moxa sticks, noted for their significant thermal intensity and enhanced penetrative capacity. Owing to its extensive contact area and unique herbal composition, Jianqiao ancient moxibustion is theoretically posited to exert superior effects in regulating yin-yang, nourishing qi and blood, and unblocking meridians. Considering the theoretical advantages of Jianqiao ancient moxibustion and the inherent limitations of moxa box moxibustion, this study proposes a randomized controlled superiority trial to compare their clinical efficacy in patients with CFS exhibiting a spleen–kidney yang deficiency pattern.

**Table 1 tab1:** Authentic Chinese medicinal materials of “Southern herbs and Northern moxa”.

Category	Place of origin	Composition
“Southern herbs” (“Jian Shiba”)	Jianqiao Area, Shangcheng District, Hangzhou	Scrophularia ningpoensis (Radix Scrophulariae) *Ophiopogon japonicus* (Radix Ophiopogonis) Rehmannia glutinosa (Radix Rehmanniae) Mentha haplocalyx (Herba Menthae) *Cassia obtusifolia* (Semen Cassiae) *Euphorbia lathyris* (Semen Euphorbiae) Angelica dahurica (Radix Angelicae Dahuricae) *Brassica alba* (Semen Sinapis) Schizonepeta tenuifolia (Herba Schizonepetae) *Arctium lappa* (Fructus Arctii) *Lycopus lucidus* (Herba Lycopi) *Ricinus communis* (Semen Ricini) *Benincasa hispida* (Semen Benincasae) *Benincasa hispida* (Exocarpium Benincasae) *Raphanus sativus* (Semen Raphani) *Raphanus sativus* (Dried Radish Root) Eupolyphaga sinensis (Eupolyphaga) *Bombyx mori* (Bombyx Batryticatus)
“Northern moxa”	Nanyang, Henan	Moxa (Artemisia argyi)

## Methods

2

### Trial design

2.1

This study is a single-center, single-blind, randomized controlled superiority trial. A total of 90 eligible participants diagnosed with CFS with a spleen–kidney yang deficiency pattern will be enrolled. Participants will be randomly assigned in a 1:1 ratio to receive either Jianqiao ancient moxibustion or moxa box moxibustion. The study will span 16 weeks, comprising a 4-week treatment period and a subsequent 12-week follow-up phase.

The trial is registered with the Chinese Clinical Trial Registry (ChiCTR2300079165). The trial flowchart is illustrated in Figure 1, and a detailed timeline is provided in Table 2.

**Figure 1 fig1:**
[figure not shown]
Flowchart of the trial.

**Table 2 tab2:** Trial schedule.

Time point	Study period			
	Pre-treatment (Baseline) Week 0	Treatment Weeks 1–4	Post-treatment week 4	Follow-up week 16
Assessment of eligible				
Inclusion criteria	√	—	—	—
Exclusion criteria	√	—	—	—
Randomization				
Allocation	√	—	—	—
Intervention				
Jianqiao ancient moxibustion treatment	—	√	—	—
Moxa box moxibustion treatment	—	√	—	—
Primary outcome				
Fatigue Scale-14 (FS-14)	√	—	√	√
Secondary outcomes				
The Symptoms scale of Spleen–Kidney Yang Deficiency	√	—	√	√
Self-rating depression scale (SDS)	√	—	√	√
Self-rating anxiety scale (SAS)	√	—	√	√
Infrared thermal imaging detection	√	—	√	√

### Study setting

2.2

This trial will be conducted at the Department of Acupuncture and Moxibustion at The Third Affiliated Hospital of Zhejiang Chinese Medical University. The department maintains a robust clinical patient volume, ensuring adequate participant recruitment. All study participants will be recruited from the inpatient and outpatient populations of this department. This prospective clinical trial is scheduled to take place from 1 January 2024 to 30 November 2026.

### Research hypothesis

2.3

Primary hypothesis: Participants receiving Jianqiao ancient moxibustion will demonstrate significantly greater improvement in fatigue severity than those in the moxa box moxibustion group.

Secondary hypothesis: Participants in the Jianqiao ancient moxibustion group will exhibit significantly greater improvements in TCM syndrome scores and reductions in anxiety and depression levels. In addition, favorable alterations in the infrared thermal characteristics of the Sanjiao and Governor Vessel are expected.

### Study participants

2.4

#### Diagnostic criteria

2.4.1

Western Medical Diagnostic Criteria. The diagnostic criteria for CFS are formulated according to the 1994 Centers for Disease Control and Prevention (CDC) guidelines (9):(1) Patients suffer from unexplained persistent or recurrent chronic fatigue, regardless of physical strain, which cannot be alleviated by rest. The fatigue has a definite onset, results in substantial impairment of occupational, educational, or personal activities, and persists for six months or longer.(2) At least four of the following symptoms occur persistently or recurrently after fatigue onset: ① impaired memory or concentration that interferes with work, study, or social activities; ② sore throat; ③ tender palpable cervical or axillary lymph nodes; ④ myalgia; ⑤ multiple joint pain without redness or swelling; ⑥ newly developed severe headache; ⑦ unrefreshing sleep; and ⑧ fatigue that cannot be relieved within 24 h after exercise.TCM Spleen–kidney Yang Deficiency Syndrome Diagnostic Criteria. These criteria are formulated according to the *Clinic Terminology of Traditional Chinese Medical Diagnosis and Treatment—Part 2: Syndromes/Patterns* (20):(1) Presence of at least three of the following five primary symptoms: ① fear of cold and cold extremities; ② lassitude and lack of strength; ③ shortness of breath and laziness to speak; ④ reduced food intake; and ⑤ soreness and weakness of the waist and knees.(2) Presence of at least two of the following six secondary symptoms: ① cold pain in the lumbar region; ② abdominal fullness and distention; ③ cold loose stools; ④ nocturia; ⑤ tooth-marked tongue; and ⑥ a deep, feeble pulse.

#### Inclusion criteria

2.4.2

The inclusion criteria for this study are as follows:

Meeting the Western medical diagnostic criteria for CFS.Meeting the TCM diagnostic criteria for consumptive disease exhibiting a spleen–kidney yang deficiency pattern.Being aged 18–70 years, irrespective of gender.Providing voluntary, written informed consent prior to participation.Being free of severe organic diseases affecting major physiological systems.Not receiving medication or participating in other clinical trials during the study period.

#### Exclusion criteria

2.4.3

The exclusion criteria for this study are as follows:

Failure to meet the aforementioned Western medical or TCM diagnostic criteria.Presence of primary organic, endocrine, neurological, or psychiatric diseases that could otherwise account for chronic fatigue.History or presence of severe visceral, hematological, or immune system diseases, or malignant tumors.Current use of other related treatments or concurrent enrollment in other clinical trials.Women who are pregnant, lactating, or planning to conceive during the trial period.Presence of cognitive impairment, severe mental disorders, alcohol or drug abuse, or anticipated poor compliance with the study protocol.Presence of skin lesions, infection, or allergies at the targeted moxibustion sites, or scar constitution incompatible with moxibustion therapy.

#### Elimination criteria

2.4.4

Mis-enrolled participants who do not meet the inclusion criteria.Participants with incomplete data or those who commit serious protocol violations that compromise the efficacy assessment.Participants demonstrating poor compliance, those who voluntarily withdraw, or those who utilize unauthorized alternative or prohibited treatments during the trial.Trial termination due to severe adverse reactions or complications.

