### Randomization

2.5

This study will employ simple randomization to group participants. A third-party statistician will utilize SPSS version 22.0 to generate the randomization sequence, ensuring that researchers remain blinded to it. The random numbers are securely sealed in sequentially numbered opaque envelopes and stored in a double-locked cabinet. Upon completion of the baseline assessment and receipt of written informed consent, the envelopes will be opened sequentially in the order of enrollment to reveal group allocation. The allocation sequence will be maintained in strict confidentiality to prevent prediction of subsequent participants’ assignments.

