### Statistical analysis

2.12

To mitigate subjective bias, all statistical analyses will be conducted independently by two blinded statisticians utilizing SPSS version 22.0. These statisticians will remain uninformed of group allocations and intervention specifics. The intention-to-treat (ITT) analysis set will include all randomized participants who complete the baseline assessment and receive at least one intervention session, and this set will be used for the primary efficacy analysis. The per-protocol (PP) analysis set will include subjects with good treatment adherence, no significant protocol deviations, and complete outcome data and will be utilized for sensitivity analysis to assess the robustness of the research findings. Data collected at multiple time points will be analyzed using a mixed-effects model for repeated measures, including group, time, and their interaction effects, to evaluate inter-group and temporal differences. Missing data will primarily be addressed through multiple imputation, supplemented by the last observation carried forward method for sensitivity analysis, to minimize bias resulting from data attrition. Covariates such as age, sex, disease duration, and baseline FS-14 scores will be adjusted for in the model to correct for confounding bias due to baseline imbalances. The Bonferroni correction will be employed to adjust for multiple comparisons, thereby controlling for the inflation of Type I error rates associated with simultaneous evaluations of multiple secondary outcomes. Treatment adherence will be quantified as the ratio of sessions actually completed to the total number of sessions planned; statistical comparisons of adherence between groups will be conducted, supplemented by additional sensitivity analyses stratified by adherence status. Continuous data exhibiting normal distribution will be analyzed using the *t*-test, whereas data not conforming to a normal distribution will be assessed via non-parametric rank-sum tests. Categorical variables will be compared using the chi-square test or Fisher’s exact test, as appropriate. All statistical tests will be two-tailed, with a significance threshold set at *a p*-value of < 0.05.

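### Sections 2.4.4 and 2.12 are unreconciled: the elimination criteria list randomised participants whom the primary ITT analysis includes and imputes

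*Protocol article*

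**What the plan says.** Protocol article, section 2.4.4 (Elimination criteria), has four items. The first concerns mis-enrolment. The second is "Participants with incomplete data or those who commit serious protocol violations that compromise the efficacy assessment". The third is "Participants demonstrating poor compliance, those who voluntarily withdraw, or those who utilize unauthorized alternative or prohibited treatments during the trial". The fourth is "Trial termination due to severe adverse reactions or complications". The section does not say whether elimination means stopping treatment, leaving the trial or removal from an analysis, and it names no analysis set.

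Section 2.5 (Randomization) fixes the timing: "Upon completion of the baseline assessment and receipt of written informed consent, the envelopes will be opened sequentially in the order of enrollment". Compliance, withdrawal, prohibited treatment and missing follow-up scores therefore all arise after allocation.

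Section 2.12 (Statistical analysis) defines the primary population: "The intention-to-treat (ITT) analysis set will include all randomized participants who complete the baseline assessment and receive at least one intervention session". It adds that "Missing data will primarily be addressed through multiple imputation", with last observation carried forward as a sensitivity analysis. The per-protocol set, which requires good adherence, no significant deviations and complete outcome data, is reserved for sensitivity analysis. The section also compares adherence between groups and plans sensitivity analyses stratified by adherence.

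**The concern.** The same participant is treated in two ways. Someone who attends one session and then withdraws is eliminated under section 2.4.4, but under section 2.12 belongs to the primary set with missing scores imputed. The protocol gives no rule for deciding which section governs.

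This matters more here than in a double-blind trial. Section 2.6 states that participants and practitioners cannot be blinded, and the primary outcome, the FS-14, is a patient questionnaire. Staying in treatment, withdrawing or seeking other treatment can depend on both the arm and the response. If such patients leave the primary comparison, the arms compared are no longer those formed by randomisation. If elimination also stops week-4 and week-16 assessments, calling the set ITT does not recover the lost data. A choice between the two sections made after the data are seen would let the primary population be picked with results in view.

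**Working it through.** **1. The two sections side by side**

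| Participant | Section 2.4.4 | Section 2.12 |
|---|---|---|
| Incomplete data | eliminated | in ITT, values imputed; outside per-protocol |
| Serious violation | eliminated | in ITT; outside per-protocol |
| Poor compliance | eliminated | in ITT, and needed for the adherence analyses; outside per-protocol |
| Withdraws after at least one session | eliminated | in ITT, values imputed |
| Prohibited treatment | eliminated | in ITT; outside per-protocol if a significant deviation |

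If section 2.4.4 governed the primary set, eliminating incomplete data would leave nothing for multiple imputation to do, and eliminating poor compliers would undercut the adherence analyses.

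**2. The plan's own figures (section 2.11)**

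Inputs: post-treatment FS-14 of 4.86 ± 1.43 and 6.23 ± 2.73, two-sided α 0.05, power 0.80, dropout 10%.

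- Difference = 6.23 − 4.86 = 1.37.
- Pooled SD = √((1.43² + 2.73²)/2) = 2.18.
- d = 1.37/2.18 = 0.63, as stated.
- n per arm = 2(1.960 + 0.842)²/0.63² = 39.6, so 40, as stated.
- 40/0.9 = 44.4, so 45 per arm and 90 in total, as stated.

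The sample size reproduces and is not affected by this point.

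**3. Illustration: what if elimination reached the primary set?**

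The document gives no elimination rate by arm and no link between elimination and outcome, so what follows rests on assumptions. Suppose there is no true effect. In one arm a fraction f is removed according to a propensity that correlates ρ with a worse FS-14 score. In the other arm removal is random.

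Shift in the selected arm's mean = ρ × SD × φ(z_f)/(1 − f).

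- At f = 0.10, the planned loss: φ(z_f) = 0.1755, and 2.18 × 0.1755/0.9 = 0.425.
- ρ = 0.3 gives 0.13 points; ρ = 0.5 gives 0.21 points. These are 9% and 16% of the 1.37-point planning difference.
- Standard error at 40 per arm = 2.18 × √(2/40) = 0.487.
- Shift divided by standard error = 0.26 and 0.44.
- Two-sided type I error = 1 − Φ(1.96 − 0.26) + Φ(−1.96 − 0.26) = 5.8%. With 0.44 in place of 0.26 it is 7.2%.

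**4. Dependence on the assumptions**

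- Same rate and same mechanism in both arms, no treatment effect: the two shifts cancel, the bias is 0 and type I error stays at 5%.
- A different model, with eliminated patients 0.5 to 1 SD worse than retained ones and elimination of 10% in one arm and 20% in the other, starting from 45 per arm: bias = (0.20 − 0.10) × 0.5 to 1 SD = 0.05 to 0.10 SD, or 0.11 to 0.22 points; type I error 5.5 to 7.2%. The 20% rate is assumed.

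**5. Direction**

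A higher FS-14 score means worse fatigue. Removing worse-scoring patients lowers the mean of the arm that loses them, so the bias flatters that arm.

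**The case against.** The strongest reply is that section 2.12 already answers the question. It assigns the primary efficacy analysis to the ITT set. The elimination list closely resembles the per-protocol definition, and the imputation and adherence analyses make sense only if the affected participants are kept. On this reading section 2.4.4 lists per-protocol exclusions or withdrawals, and only a cross-reference is missing.

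Much of this stands. A reader might infer that the plan does drop these patients from the primary analysis, and so that the primary result will be biased. The document does not say that, and if section 2.12 is followed and outcomes are still collected, this bias does not arise. What does not stand is the claim that the reading is settled. Section 2.4.4 sits under Study participants, names no set, refers to the effect on the efficacy assessment, and is never mentioned in section 2.12. These are two stated rules in conflict, not a detail left to a later analysis plan.

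Three further inferences are tempting and should not be drawn:

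- **Later medication as mis-enrolment.** The item "Mis-enrolled participants who do not meet the inclusion criteria" could be combined with the inclusion criterion "Not receiving medication or participating in other clinical trials during the study period" so that a medicine taken after randomisation makes a patient mis-enrolled. Mis-enrolled ordinarily means wrongly entered, and prohibited treatment during the trial has its own item, which would then be largely redundant.
- **Loss of safety data.** The adverse-reaction item is worded as termination and may be only a discontinuation rule. Section 2.9 has adverse events documented at every treatment and assessment visit, and nothing removes anyone from safety reporting.
- **Bias towards the better-tolerated arm.** Under the model above the opposite holds: the arm that loses its dissatisfied or worse-scoring patients gains.

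**Conclusion.** The point holds as an unreconciled conflict between sections 2.4.4 and 2.12 over who is in the primary comparison. It does not hold as a finding that the primary comparison is biased. Bias requires that elimination reach the primary set or end outcome collection, and also that removal differ between arms in rate or prognosis.

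The document does not allow its size to be derived. The figure of 0.13 to 0.21 FS-14 points, with type I error of about 6 to 7%, rests on SD 2.18, the planned 10% loss, an assumed correlation of 0.3 to 0.5 and selective removal in one arm only. Nothing in the protocol supports that asymmetry or that correlation, and with symmetric removal and no treatment effect the bias is zero. The case for settling the matter before analysis rests on the conflict itself, in an open-label trial with a patient-reported primary outcome, and on how little the repair costs.

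**What to change.** In section 2.4.4, state that:

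- the elimination criteria define exclusion from the per-protocol set only;
- participants who meet them stay in the ITT set as randomised;
- their week-4 and week-16 outcomes are still collected unless consent to follow-up is withdrawn;
- missing values are multiply imputed as section 2.12 already states.

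Add a reference to section 2.4.4 in the per-protocol definition of section 2.12. Reconcile the item on termination for severe adverse reactions with section 2.12 by stating what happens to those participants' data, leaving any treatment-stopping rule as it is.

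The cost is a few sentences and the continued follow-up of participants who stop treatment. The sample size stays at 90.
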